### Method of inclusion

Patients will be recruited from six collaborating hospitals. An experienced senior consulting orthopaedic surgeon at the local department will classify the radiographs before electronically transmitting them to the study center (OUS Orthopaedic Department), where another consulting orthopedic surgeon experienced in skeletal traumatology will confirm radiographs and inclusion in the trial before randomization and allocation to treatment.

Allocation to treatment will take place after thorough oral and written information to the patient, and signed consent. Electronic randomization will be performed by a dedicated doctor at each hospital, and by means of a secured web-solution made by NTNU WebCRF system, with approval from the OUS Head of Patient Security (https://webcrf.medisin.ntnu.no/client/index.php).

### The inclusion criteria

Patients aged 65 or older admitted to hospital with a displaced three- or four part proximal humerus fracture of OTA/AO group 11-B2 or 11-C2 (displaced fracture of extra-articular or articular, bifocal type) [19]. The subgroups -.1, -.2 and -.3 will be included for both B2 and C2 groups, provided severe displacement, defined as a mal-position of at least 45° of angular deviation in valgus or 30° in varus in true frontal projection, regardless of whether the fracture is impacted or not. Fracture with more than 50% displacement of the head against the metaphysis (surgical neck) will also meet the criteria. The greater or lesser tubercles must be displaced in a three- or four part fracture, the degree of displacement is not critical for inclusion.

### Exclusion criteria

Patient younger than 65 years or older than 85 years. Previous history of injury or illness of the injured or contra-lateral shoulder, injuries of other parts of the humerus or the contra-lateral upper extremity, alcohol- or drug abuse, dementia, neurological diseases, or severe cardiovascular or lung diseases that would contraindicate surgery. Patients must understand the Norwegian language and be compliant to rehabilitation and follow-ups. A fracture or severe deformity of the glenoid should not appear in a pre-operative CT-scan of the shoulder.

### Ethics and safety

The study has been approved by the Regional Committee of Research, Health Region Southeast, Oslo, Norway at November 6^th^ 2012 (Reference 2012/1606).

Patients will be included after thorough oral and written information in accordance with regional ethic committee approval. All patients must give their written consent.

A study specific participant’s number and code referring to their hospitals will identify the participants. Patient name and other identifiable details will not be included in any electronic study data file. Any patient related data transferred between the main study group at OUS and participating sites will be identifiable only by the patients unique study number.

### Outcome parameters

Functional score of both shoulders, QoL interviews (15D) as well as health economic evaluation will be performed by an independent physiotherapist blinded to the treatment. Self-assessment score (Oxford shoulder score) will be included at each follow-up.

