## Methods/Design

### Study design

The design of the study is a multi-centre randomized controlled trial (RCT). Patients admitted to hospital with a displaced proximal humeral fracture in need of surgical treatment will be randomly allocated to two groups; Intervention group or control group. The design is semi-blinded for independent physiotherapists interviewing and testing the patients at three and six months, thereafter at one, two and five years.

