### Economic evaluation

Cost data in this study will include costs incurred in hospital and subsequently, including time spent in operating theatre, hospital consumables, rehabilitation stays, subsequent hospital stay, help at home, consultations of NHS care (General practitioners, physiotherapists, district nurses etc.), transportation and sick-leave. Information for estimating costs will be collected from the patient by a questionnaire at each follow-up. Health-utility data will be obtained from the HS15D [63] (Additional file 1).

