### Clinical follow-ups and blinding

The clinical follow-ups will take place at 3 and 6 months, one, two and five years. An independent physiotherapist will perform Constant scoring and assist the patients with a 15D QoL-questionnaire at these follow-ups. The physiotherapist will be blinded to the treatment and shall not take active part in the patient treatment of either group. The postoperative exercises and prescribed self-training program will be explained to patients by another physiotherapist before they are discharged from the hospital.

At every follow-up all patients will wear a T-shirt to cover their shoulders during examination by the physiotherapist performing the shoulder test. The patients will be thoroughly instructed not to tell the physiotherapist about their treatment.

Patients will complete the OSS and ASES self-assessment form at 6 months, one, two and five years follow-ups. Radiographic examination will be performed at every follow-up.

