## Discussion

This protocol has been designed according to recommendations given by the Consort group [4]. The design of a randomized controlled study with a high level of evidence including more than 100 patients, with semi-blinded independent physical therapists collecting patient data gain important knowledge about proximal humeral fractures. A standardized surgical approach for both groups without compromising the deltoid muscle, reduces group differences, and a standarized educational program for all physiotherapists prior to examination of patients at follow-up contribute to a better methodological design and strengthen this study.

This study protocol has been adjusted according to our experience from former studies, both regarding outcomes, method of randomization and exclusion criterias [16, 17]. Also, to gain knowledge of the external validity of this study, all patients aged 65 to 85 years admitted to two of the recruiting hospitals will be grouped according to the exclusion criteria and AO classification, hopefully increasing our knowledge of the generalizability of our results. This generalizability and the question if the results of this trial will cause impact in the future treatment of displaced B2 and C2 proximal humeral fractures is a basic issue when a new trial is designed. Although it is more than 40 years since Charles Neer wrote his two important papers on classification and treatment of proximal humeral fractures, these papers are still frequently referred and the treatment is still under debate [1, 2]. The sparse number of studies at the highest level of evidence may be one of the reasons.

The trial may have potential weaknesses: Blinding of a trained physiotherapist examining a patient with a prosthetic replacement is difficult due to the mechanics of the implant. Another potential problem is that the primary outcome (Constant score) has a low reproducibility between different observers in a multicenter trial [67, 68]. However, the pre-trial training for all participating physiotherapists will reduce this bias.

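### The blinded physiotherapist who rates the Constant score is also given the health economic evaluation, which opens an avoidable route to unmasking

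*Protocol article*

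**What the plan says.** Four sections of the protocol article bear on this.

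- **Outcome parameters** gives functional scoring of both shoulders, the 15D interviews and the economic evaluation to one role: "as well as health economic evaluation will be performed by an independent physiotherapist blinded to the treatment".
- **Clinical follow-ups and blinding** gives that role the primary outcome: "An independent physiotherapist will perform Constant scoring and assist the patients with a 15D QoL-questionnaire at these follow-ups". It does not mention costs. Its safeguards are that the assessor takes no part in treating either group, that a T-shirt covers the shoulder, and this: "The patients will be thoroughly instructed not to tell the physiotherapist about their treatment".
- **Economic evaluation** lists the cost items, "including time spent in operating theatre, hospital consumables, rehabilitation stays, subsequent hospital stay, help at home, consultations of NHS care", and names physiotherapists among the care contacts. It adds: "Information for estimating costs will be collected from the patient by a questionnaire at each follow-up".
- **Study design** describes the contact with patients: "The design is semi-blinded for independent physiotherapists interviewing and testing the patients at three and six months". The visits at one, two and five years follow in the same sentence.

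The Discussion admits one limit on blinding: "Blinding of a trained physiotherapist examining a patient with a prosthetic replacement is difficult due to the mechanics of the implant". It does not mention the cost data.

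**The concern.** The assessor is meant to stay ignorant of treatment, yet as written the same person is assigned an evaluation of what care the patient has needed since surgery. A patient asked about another hospital stay will naturally say why it happened, and the reason can identify the implant.

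The Constant score is rated by an observer, and the Discussion concedes that it reproduces poorly between observers. An assessor who knows the arm can shift the rating without intending to. Disclosure through readmission would also fall mainly on patients whose treatment went badly, so the resulting error need not be equal in the two arms and need not cancel in the comparison.

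**Working it through.** **1. Is it the same person?** Outcome parameters assigns the functional score and the economic evaluation to a blinded independent physiotherapist. Clinical follow-ups and blinding has the blinded independent physiotherapist do the Constant scoring. Read together, one role holds both tasks.

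**2. Is it the same visit?** Cost information is gathered at each follow-up. Constant scoring takes place at 3 and 6 months and at one, two and five years. The occasions coincide, and no section separates the tasks or says which comes first.

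**3. Can the content reveal the arm?** The cost items include "rehabilitation stays, subsequent hospital stay, help at home" and physiotherapist contacts. The section on interim analyses and stopping guidelines lists the complications to be watched:

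| Complication | Reverse prosthesis | Plate |
|---|---|---|
| Infection | yes | yes |
| Dislocation of the prosthesis | yes | – |
| Loosening of glenosphere or stem | yes | – |
| Scapular notching | yes | – |
| Screw pull-out or cut-out | – | yes |

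Only infection is shared. An admission alone does not name the arm, but its reason often would.

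**4. Does visit order alone solve it?** Not fully. Scoring first protects that day's rating. If the same physiotherapist sees the patient again, something learned at six months is still known at two years. The documents do not say whether assessors are kept constant. Keeping the form away from the assessor therefore matters more than the order.

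**5. Size.** The protocol gives no unmasking rate and no rating bias, so the bias cannot be estimated. What can be shown is how sensitive the planned comparison would be to a given bias.

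Inputs from Power of the trial and sample size: SD 18, difference 10, α 0.05, power 0.80, 51 required and 60 planned per group. The plan's own figure reproduces (two-sided, normal approximation):

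n = 2 × (1.960 + 0.842)² × 18² / 10² = 50.9, rounded up to 51 per group.

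The standard error of the difference is 18 × √(2/51) = 3.56 points at 51 per group and 18 × √(2/60) = 3.29 at 60. If there were no true effect and assessment shifted the difference by b points, the two-sided false-positive rate would be

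1 − Φ(1.96 − b/SE) + Φ(−1.96 − b/SE).

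| Assumed shift b (points) | 51 per group | 60 per group |
|---|---|---|
| 1 | 0.059 | 0.061 |
| 2 | 0.087 | 0.093 |
| 3 | 0.134 | 0.150 |
| 5 | 0.289 | 0.331 |

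The shifts are assumptions chosen to show a range. They are not estimates of what this route would cause.

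**The case against.** The strongest reply is that no cost interview is described. Economic evaluation speaks of a questionnaire, Outcome parameters attaches the word for interviewing to the 15D, and the blinding section gives the physiotherapist only Constant scoring and help with the 15D. The form may already be self-completed. This stands as a limit: the documents do not establish that the assessor questions patients about costs. It does not remove the point, because Outcome parameters states that the blinded physiotherapist performs the evaluation.

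A reader might also infer more than the text supports:

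- **That the two instructions flatly contradict each other.** They do not. A patient can report a hospital stay without naming the operation, and none of the listed cost items asks about the implant.
- **That the rehabilitation timetable gives the arm away.** Table 1 does differ by arm, with its last step at 12 weeks against 8. But the cost items concern stays and contacts, not permitted exercises, and the group comparisons are planned at two and five years. Any such cue would matter mainly at three months.
- **That assessor blinding is the only safeguard.** The assessor's non-involvement in treatment and the T-shirt are also stated, physiotherapists are trained before the trial, and the Oxford score is patient-completed.

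Two further replies deserve weight. The design is openly called semi-blinded and the implant itself may unmask the assessor, so the added effect could be small. That is fair, but the implant's mechanics cannot be changed and the routing of a form can. Form routing is also detail that an article often leaves to the full protocol. Here, however, the article does make an assignment, and it is that assignment which causes the difficulty.

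**Conclusion.** The point holds as an avoidable risk to assessor blinding; unmasking is not shown to occur. As written, the rater of the primary outcome is also assigned patient-reported data on later care, at the same visits and with no separation. This adds to the weakness the Discussion already concedes.

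The conclusion rests on two readings: that performing the evaluation brings the assessor into contact with the answers, and that patients sometimes explain why they were readmitted. If the form is already self-completed and kept from the assessor, what remains is a wording inconsistency between Outcome parameters, Economic evaluation, and Clinical follow-ups and blinding.

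The size is unknown, and no stated figure in the protocol changes. A reader might want to express the bias as a share of the 10-point difference, but that would need an unmasking rate and a rating shift that the documents do not contain. The change is worth making because it is cheap.

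**What to change.** 1. In Outcome parameters, remove the health economic evaluation from the blinded physiotherapist's tasks, and bring that section into line with Economic evaluation and Clinical follow-ups and blinding.
2. State that the patient completes the cost questionnaire alone, as already happens with the Oxford score, and returns it to existing clinic staff without the assessor seeing it.
3. State that at each visit the Constant score is completed and recorded before any other questionnaire, including the 15D with which the physiotherapist helps.

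This changes form routing and visit order only. It needs no new staff and leaves treatment, endpoints and sample size as they are. The downside is slightly more incomplete cost forms.

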### Primary outcome: Constant score

The score originally described by Constant and Murley will be used to evaluate the functional outcome [65]. Maximum score for each shoulder is 100 points. Both shoulders will be rated and presented as absolute scores (CS). In order to reduce the influence of age the difference between the scores of the injured and the uninjured shoulder will be calculated. This difference is designated CSD (Constant Score Difference). Thus, normal function on the injured side will be zero. Measurement of strength will be performed according to recommendations given by the European Society of Shoulder and Elbow Surgeons ESSSE (http://secec.org/). The highest value of three measurements will be registered for the power score. There is no established minimal clinically important difference (MCID) for the Constant score, but 10 points is often regarded as suitable, although debated [67, 68].

The “Adjusted Constant score” (ACS) for the injured shoulder will also be calculated from the CS at the injured shoulder with adjustment for age and gender as a secondary outcome [66].

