### Power of the trial and sample size

To calculate the sample size we used the primary outcome Constant Shoulder Score with a range from zero to 100 points. Using the mean values from the injured shoulder in a similar population after proximal humeral fractures, SD equals18 according to clinical experience [16, 43]. There are two groups to be compared: Intervention group and control group. The minimal clinically important difference has been decided to equal 10 points. Level of significance (α) equals 0.05. Given a power of 0.80 (β) the number required in each group is 51 patients. Due to a predicted loss of included patients during follow-up, we aim to include 60 patients in each group.

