### Statistics

Statistical analyses will be performed with the SPSS 17.0 software or later version (SPSS Inc. Chicago, Illinois, USA). All outcomes will be reported as mean values and 95% confidence interval (95% CI) for both treatment groups and for each hospital separate, as well as for all hospitals together. In case of small data groups, bootstrapped 95% CI will be calcluated. Mean differences between the groups will be compared with independent *t*-test and Mann–Whitney test as appropriate at two and five years follow-up. Subgroup analyses for the two fracture groups B2 and C2 are planned to gain further information of effectiveness of treatment. Multiple imputation will be used to handle missing values. The QALY analysis from 15D outcome will be performed according to the specific 15D syntax for SPSS and completed with a one-way sensitivity analysis for each variable in the analysis.

The intention-to-treat principle will be adopted: Patients will be analysed according to their initial treatment group in case of cross over to the other group.

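### The plan does not say whether the Constant score or the side-to-side difference is tested; regression on the uninjured-shoulder score would settle this and is at least as precise as either

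*Protocol article*

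**What the plan says.** All of this is in the protocol article.

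- **Primary outcome: Constant score.** The section first gives the absolute score: "Both shoulders will be rated and presented as absolute scores (CS". It then adds CSD, with the aim of reducing the influence of age: "the difference between the scores of the injured and the uninjured shoulder will be calculated". Only the age- and gender-adjusted score (ACS) is ranked lower, being calculated "with adjustment for age and gender as a secondary outcome". Nothing ranks CS against CSD.
- **Hypothesis.** It is stated on the Constant shoulder score, at two and five years.
- **Power of the trial and sample size.** "we used the primary outcome Constant Shoulder Score with a range from zero to 100 points". The spread is that of the injured side: "Using the mean values from the injured shoulder in a similar population after proximal humeral fractures, SD equals18 according to clinical experience". With a difference of 10 points, alpha 0.05 and power 0.80, the section arrives at 51 per group, raised to 60 for loss to follow-up.
- **Statistics.** "Mean differences between the groups will be compared with independent" t-test or Mann–Whitney test, at two and five years. No covariate is named.
- **Method of randomization.** Allocation is stratified by age and gender within each hospital.
- **Clinical follow-ups and blinding.** Constant scoring takes place at the follow-up visits, so the uninjured-shoulder score is a post-randomisation measurement.

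**The concern.** The uninjured shoulder is each patient's own reference for normal function and is scored at the same visits. It can be used in three ways: ignored (raw CS), subtracted (CSD) or entered as a covariate. These have different variances, and the article leaves open which of the first two is meant.

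Subtraction fixes the regression slope of the injured score on the uninjured score at 1. If the true slope is lower, it over-corrects and brings in noise from the second measurement. With a weak enough correlation, CSD is noisier than the unadjusted score, so a step intended to reduce age-related variation would instead add variation. If CS is tested, that problem goes away, but a score already collected and a stratification factor (age) are both left out of the primary comparison.

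What is at stake is efficiency and a fixed endpoint, not bias. With about 51 evaluable patients per group and nominal power of 80%, there is little to spare.

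**Working it through.** **Inputs from the article:** difference 10 points, SDy = 18 (injured shoulder), alpha 0.05 (two-sided reproduces the stated n; one-sided would give 41), power 0.80, 51 per group.

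**Assumed, because the article gives neither:** k = SDx/SDy, the ratio of the uninjured to the injured SD, from 0.5 to 1; and rho, the correlation between the shoulders at the same visit, from 0.2 to 0.7.

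**Step 1. Reproduce the plan's figure.** n = 2 × [18 × (1.96 + 0.84)/10]² = 50.86 with unrounded normal quantiles, so 51 per group. The t-distribution version gives 51.8. Power at 51 per group is 79.3% by the noncentral t (80.1% by the normal approximation). The stated number is therefore right for the absolute injured-shoulder score.

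**Step 2. Variances.** If treatment does not affect the uninjured shoulder, all three analyses estimate the same 10-point difference, and only the residual variance changes.

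- Raw CS: SDy²
- CSD: SDy² + SDx² − 2·rho·SDx·SDy = SDy²(1 + k² − 2·rho·k)
- CS with the same-visit uninjured score as covariate: SDy²(1 − rho²)

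CSD minus covariate = SDx² − 2·rho·SDx·SDy + rho²·SDy² = (SDx − rho·SDy)², which is never negative. It is zero when k = rho, that is, when the true slope rho/k equals 1.

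CSD exceeds raw CS when SDx² > 2·rho·SDx·SDy, that is, when rho < SDx/(2·SDy) = k/2. The break-even correlation is 0.25 at k = 0.5, 0.375 at k = 0.75 and 0.50 at k = 1.

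**Step 3. Power at 51 per group** (noncentral t; raw CS is 79% throughout)

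| k | rho | SD of CSD | Power, CSD | SD with covariate | Power, covariate |
|---|---|---|---|---|---|
| 0.5 | 0.2 | 18.4 | 77% | 17.6 | 81% |
| 0.5 | 0.3 | 17.5 | 81% | 17.2 | 83% |
| 0.5 | 0.5 | 15.6 | 89% | 15.6 | 89% |
| 0.5 | 0.7 | 13.3 | 96% | 12.9 | 97% |
| 0.75 | 0.2 | 20.2 | 70% | 17.6 | 81% |
| 0.75 | 0.3 | 19.0 | 75% | 17.2 | 83% |
| 0.75 | 0.5 | 16.2 | 87% | 15.6 | 89% |
| 0.75 | 0.7 | 12.9 | 97% | 12.9 | 97% |
| 1 | 0.2 | 22.8 | 59% | 17.6 | 81% |
| 1 | 0.3 | 21.3 | 65% | 17.2 | 83% |
| 1 | 0.5 | 18.0 | 79% | 15.6 | 89% |
| 1 | 0.7 | 13.9 | 95% | 12.9 | 97% |

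Example, k = 1 and rho = 0.3: the CSD factor is 1 + 1 − 0.6 = 1.4, so SD = 18 × √1.4 = 21.3. The covariate factor is 1 − 0.09 = 0.91, so SD = 18 × √0.91 = 17.2.

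By the plan's own formula with k = 1, CSD needs 82 per group at rho 0.2, 72 at 0.3, 51 at 0.5 and 31 at 0.7. The covariate analysis needs 49, 47, 39 and 26.

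**Step 4. Cost of estimating the slope.** Simulation with 51 per group, SDx = 18 and rho = 0.3 gave standard errors of the treatment effect of 3.61 (raw), 4.28 (CSD) and 3.47 (covariate). Where the true slope is 1 (SDx = 10, rho = 0.56), CSD gave 2.94 and the covariate analysis 2.95. The finite-sample cost is under 1%.

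**The case against.** **CSD may not be the tested endpoint.** A reader might infer that CSD is the primary outcome and that the trial is therefore underpowered. The text does not establish this. The section is headed by the Constant score, the hypothesis names that score, the sample size uses the 0–100 scale with the injured-shoulder SD, and the Statistics section does not mention CSD. Its mean differences are between groups, not between sides. This objection stands. What remains is that CS and CSD sit side by side under the primary outcome without a choice between them.

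**No loss is shown.** Neither k nor rho is in the article. Previous injury or illness of the contralateral shoulder is an exclusion, which makes a smaller spread on that side plausible. At k = 0.5 the two analyses are within 4 points, and from rho = 0.3 upward CSD beats raw CS. This also stands.

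**The precision result is narrow.** It holds for the uninjured score from the same visit that CSD subtracts. It does not hold for a 3-month score used at two or five years: with k = 1, CSD at a same-visit rho of 0.7 has 95% power, whereas an earlier score correlating 0.5 gives 89%. Nor does it hold against adjustment for age alone: with an assumed age correlation of 0.3 the residual SD is 17.2 (47 per group), while CSD with SDx = 10 and rho = 0.6 has SD 14.4 (33 per group). The article also claims only to reduce the influence of age, not to remove it.

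**Age is handled elsewhere, and covariates belong in the analysis plan.** Age is a stratification factor, and ACS adjusts for it as a secondary outcome. Neither puts age into the primary comparison. A fuller plan could add covariates, but the article does name the test, and that test is unadjusted.

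**Conclusion.** The point holds as a matter of endpoint definition and efficiency. The article fixes an unadjusted test without saying whether it applies to CS or CSD, and its SD of 18 and 51 per group are justified for CS only. Whichever was meant, regression on the same-visit uninjured score is at least as precise, apart from a negligible cost of estimating the slope.

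Over the assumed range, power at 51 per group is 59% to 97% for CSD, 79% for raw CS and 81% to 97% with the covariate. The gain over CSD is at least 5 points at rho of 0.3 or less with k of 0.75 or more, and at rho = 0.5 with k = 1. It is small where k is near rho. The conclusion rests on an SD of 18, a 10-point difference and no effect of treatment on the uninjured shoulder.

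It would go too far to say that the trial has lost power through CSD, or that either choice biases the result. The documents support neither claim.

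**What to change.** 1. In the primary outcome section, name the injured-shoulder Constant score as the primary endpoint, and label CSD as descriptive or secondary. It keeps its use as a measure of distance from normal function.
2. In the Statistics section, replace the unadjusted primary comparison with a linear regression of the injured-shoulder score on treatment, with the uninjured-shoulder score from the same visit and the stratification factors age, gender and hospital as covariates. Do not substitute the 3-month uninjured score, for which the precision result does not hold.
3. Add a sensitivity analysis with the stratification factors only.
4. In the sample size section, state that the SD of 18 refers to the unadjusted injured-shoulder score. The 51 per group then stands for the raw score, and any gain from adjustment comes on top.

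**Cost.** Wording only, since both shoulders are already scored. The headline becomes an adjusted difference in Constant points. The uninjured score is measured after randomisation, so treatment must be assumed not to affect that shoulder. CSD already makes this assumption, and the sensitivity analysis in item 3 avoids it.
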